## Methods

### Design

The current study is a single-blind, cluster-randomised controlled feasibility trial of COB-MS (see “Interventions”). The structure is based on the Medical Research Council’s (MRC’s) “Framework for development and evaluation of RCTs for complex interventions to improve health” [27]. This study will use a treatment as usual, wait-list control group design and a pre-post study design with two additional follow-up testing times: 12 weeks and 6 months follow-up (i.e. four data points). Follow-up data will be collected to evaluate the sustainability of intervention gains, if evident, as well as to gather data on retention over the entire duration of the trial. Fidelity and qualitative data will also be collected to inform the feasibility assessment of this trial.

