#### Sample size

As this is a feasibility study, a formal sample size calculation to evaluate the clinical effectiveness of COB-MS is not required. Instead, a pragmatic approach is adopted. It is aimed at examining the rate of retention of participants during the intervention and follow-up periods and is based on an average recruitment rate for National Institute for Health Research [28]-funded randomised controlled trials (RCTs). A 9% attrition rate is likely to occur [26]; therefore, if this were an individually randomised trial (at the patient level), a sample of 90 participants would allow for estimation of a retention rate of 91% with a 95% confidence interval (CI) of width equal to 13%. After allowing for clustering, assuming 8 participants per cluster (occupational therapist) and an intracluster correlation coefficient (ICC) = 0.05, the sample size becomes 90 × [1 + (8–1) × 0.05] = 121. Thus, the number of occupational therapists needed is 121/8 = 15. A final sample size of 15 × 8 = 120 people with MS is deemed large enough to provide information regarding the practicalities of a potential definitive randomised trial. This follows Consolidated Standards of Reporting Trials (CONSORT) guidelines for sample size calculation in feasibility studies. See Fig. 1 for the CONSORT flowchart of study participants.

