#### Gender issues

A number of different gender issues are relevant to this trial because of the condition (MS) under study, including the ratio of prevalence, age of onset, disease progression, ability to cope and quality of life issues. Data on gender will be collected and will be accounted for in analysis. Statistics, tables, figures and descriptions will focus on relevant gender differences that came up in the course of the project. Findings from this analysis will be included in the final publication. As qualitative data are being collected, the specific impact of the intervention on both male and female participants can be explored in depth. Interviews will allow participants to discuss aspects that are of importance to their own lives, which may or may not be specific to gender. Recruitment will not be gender-balanced, as this is not reflective of the population demographic. Groups (control/intervention) will be balanced, and a representative population will be recruited, if possible.

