### Measures

#### Primary outcome

*Goal attainment scaling* [31] allows participants to set meaningful goals relating to daily life which can be measured in a systematic way. This technique has shown excellent inter-rater reliability (*r* = 0.95) and construct validity (*r* = 0.92) in cognitive rehabilitation [32]. Goal attainment scaling shows reliability, validity and sensitivity when utilised within a population of adults and older people [33]. The primary endpoint will be at the 12 weeks follow-up.

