### Statistical analysis

Data analysis and reporting will follow 2010 CONSORT guidelines. The feasibility outcomes, recruitment rate, acceptability of COB-MS, rate of unblinding, retention rate and randomisation methods will be reported descriptively and narratively. Analysis will take place once all data have been collected. Means and standard deviations (or medians and interquartile range [IQR] as appropriate) will be used for continuous variables, and counts and percentages for categorical outcomes. The retention rate will be estimated using a 95% confidence interval (CI). Estimates (mean and standard deviations) of the primary outcome variable (i.e. goal attainment scaling), at week 12, will inform sample size calculations of a future definitive trial. Data resulting from primary and secondary outcome measures will be evaluated, per protocol, in terms of preliminary efficacy through a series of 2 (condition) × 4 (time) mixed (multivariate) analyses of variance as well as through correlational analysis. No analysis of health economics or cost-effectiveness will take place in this feasibility study.

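### The only named efficacy analysis, a 2 × 4 mixed (M)ANOVA, does not estimate the arm difference in goal attainment at 12 weeks, which is the stated primary endpoint

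*Protocol article*

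**What the plan says.** The Primary outcome section of the protocol article names goal attainment scaling and fixes one time point: "The primary endpoint will be at the 12 weeks follow-up". The Abstract agrees.

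The Design section describes a pre-post design with "two additional follow-up testing times: 12 weeks and 6 months follow-up (i.e. four data points"), so baseline is one of the four occasions.

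The Statistical analysis section names one between-arm efficacy method. It states "Data resulting from primary and secondary outcome measures will be evaluated, per protocol, in terms of preliminary efficacy" and continues "through a series of 2 (condition) × 4 (time) mixed (multivariate) analyses of variance as well as through correlational analysis". It names no contrast at 12 weeks. The same section plans a 12-week summary of GAS for another purpose: "Estimates (mean and standard deviations) of the primary outcome variable (i.e. goal attainment scaling), at week 12, will inform sample size calculations" of a later definitive trial.

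The Sample size section expects loss to follow-up: "A 9% attrition rate is likely to occur". It also states that no formal calculation for clinical effectiveness is needed.

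**The concern.** The endpoint is a single visit, while the analysis is a test over four visits. The two tests from a 2 × 4 mixed ANOVA answer other questions. The interaction asks whether the arms' profiles differ anywhere across the four occasions. The main effect compares the arms on the average of all four, including the occasion before treatment, when no effect can exist. Neither yields the 12-week arm difference with an interval, and the interaction can be significant because of another visit.

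Two smaller matters follow from the same choice. Classical mixed ANOVA or MANOVA needs a full set of four measurements, so a person seen at 12 weeks but absent at 6 months leaves the comparison. Baseline enters as a fourth outcome rather than as a covariate, which is usually less precise.

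At stake is the quality of the preliminary estimate that a definitive trial would build on. No confirmatory test is involved.

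**Working it through.** **The plan's own figure.** The Sample size section seeks "estimation of a retention rate of 91% with a 95% confidence interval (CI) of width equal to 13"% from 90 people. An exact interval for 82/90 has width 12.8%, which rounds to 13%. Design effect: 1 + (8 − 1) × 0.05 = 1.35. Then 90 × 1.35 = 121.5, 121/8 ≈ 15 therapists, and 15 × 8 = 120. The figure reproduces and is not in dispute.

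**Inputs.** From the article: N = 120, 15 clusters of 8, ICC 0.05, 9% attrition, four occasions. Assumed, because the article gives no value: effect 0.5 SD, two-sided 5% level, equal correlation r between occasions (0.3, 0.5, 0.7), and the missing-visit patterns below. Effective sample size is 120/1.35 = 88.9, split 64:56 (8 against 7 clusters), so n₁n₀/n = 47.4 × 41.5/88.9 = 22.1.

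**1. What the main effect estimates.** A constant effect δ at the three post-baseline visits gives (0 + δ + δ + δ)/4 = 0.75δ. An effect at 12 weeks only gives 0.25δ.

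**2. What the interaction responds to.** With d the vector of arm differences in change from baseline and S its covariance under equal correlation, the noncentrality is 22.1 × d′S⁻¹d, referred to F with 3 and n − 4 degrees of freedom. For the 12-week baseline-adjusted comparison it is 22.1 × 0.25/(1 − r²).

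| Effect in SD (post, 12 weeks, 6 months) | r = 0.3 | r = 0.5 | r = 0.7 |
|---|---|---|---|
| Interaction: 0.5, 0, 0 | 49% | 65% | 88% |
| Interaction: 0.5, 0.5, 0.5 | 49% | 65% | 88% |
| Interaction: 0.25, 0.5, 0.25 | 34% | 46% | 70% |
| Interaction: 0.67, 0.5, 0.33 (fading) | 62% | 78% | 95% |
| Adjusted 12-week comparison, 0.5 SD, individual-level df | 68% | 77% | 90% |
| The same with 13 cluster-level df | 63% | 71% | 86% |

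The first two rows are equal. Under this model the interaction cannot tell an effect that has vanished by 12 weeks from one that lasts.

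**3. Who is dropped.** Completers are compared with people seen at 12 weeks.

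- Monotone dropout of 3%, 6% and 9% by the three follow-up visits: 120 × 0.94 = 112.8 seen at 12 weeks, 120 × 0.91 = 109.2 complete. About 4 people are lost unnecessarily.
- Visits missed independently at 3%: 120 × 0.97 = 116.4 against 120 × 0.97³ = 109.5, about 7 people.
- At 5%: 114.0 against 102.9, about 11 people.
- At 9%: 109.2 against 90.4, about 19 people.

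**4. Use of baseline.** The variance of an adjusted 12-week comparison relative to a change-score comparison is (1 − r²)/[2(1 − r)] = (1 + r)/2, that is 0.65, 0.75 or 0.85 at r = 0.3, 0.5 or 0.7.

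**5. Clustering.** In a simulation of 15 clusters of 8 (r = 0.5, 3% missed per visit, no true effect; therapist variance 0.05 persistent, visit-specific or both), the adjusted 12-week comparison without a therapist term rejected in 6% to 11% of runs, and a cluster-level version in about 5%. With a 0.5 SD effect the cluster-level version had 64% to 79% power. A replacement analysis therefore needs the therapist term.

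**The case against.** The best defence is that this is a feasibility trial with no efficacy power claim, that efficacy is called preliminary, that the 12-week means and SDs needed for a later sample size are planned anyway, and that a profile over time suits the stated interest in whether gains last. A follow-up contrast or a missing-data rule may also stand in an analysis plan that is not shown. This lowers the weight of the point. It does not remove it: the article does name a between-arm method, and that method is not aimed at the endpoint that the article names. Means and SDs meant for planning are not a stated between-arm estimate with an interval.

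Several stronger readings are tempting, and the documents do not support them.

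- A reader might infer that the 12-week contrast is generally more powerful. With a fading effect the interaction has 78% against 77% at r = 0.5 and 95% against 90% at r = 0.7, and the 12-week figures fall further with cluster-level degrees of freedom.
- A reader might infer that the plan deletes everyone with a missed visit. That is a property of the classical method; the article states no missing-data rule. Nor are all of the roughly 11 people behind the 9% attrition lost because of the method, since many may have no 12-week value under any analysis.
- A reader might infer that baseline is discarded. The interaction uses it through change, only less efficiently. For GAS the gain from adjustment may be small if baseline scores are fixed by construction.
- A reader might take "Data on gender will be collected and will be accounted for in analysis" as a promise of a gender term in the model. The Gender issues section speaks of descriptive reporting of differences, and the Demographic and clinical information section assigns gender to correlational analysis and interpretation. Neither promises a covariate.

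**Conclusion.** The point holds in a limited form. The named 2 × 4 (M)ANOVA does not estimate the 12-week arm difference, and its interaction can be significant because of another visit: 49% to 88% of the time in the example with no effect at 12 weeks. The mismatch between endpoint and tests rests on the article's text alone. The percentages rest on an assumed 0.5 SD effect, equal correlations of 0.3 to 0.7 and an effective sample of 89.

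The loss of people seen at 12 weeks is small under monotone dropout (about 4 of 120) and larger if single visits are missed (about 7 to 19 at 3% to 9% per visit); it applies only if the classical form is used. The baseline inefficiency is a variance ratio of (1 + r)/2 and may shrink for GAS.

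The consequence is a poorly targeted preliminary estimate, not an underpowered confirmatory test. The change is worth making, but the trial's feasibility aims do not depend on it.

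**What to change.** In the Statistical analysis section, replace the 2 × 4 (M)ANOVA with one linear mixed model per outcome, fitted to all available post-baseline visits, with:

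- arm, visit and arm × visit as fixed effects;
- the baseline value as covariate where it varies between participants;
- unstructured within-participant covariance;
- a random effect for occupational therapist;
- a small-sample degrees-of-freedom method suited to about 15 clusters.

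Name the arm difference in GAS at the 12-week follow-up, with its 95% CI, as the primary preliminary-efficacy estimate. Report the post-intervention and 6-month differences from the same model as secondary; they also serve the question of whether gains last.

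The cost is revised wording and slightly more programming; no further participants, visits or variables are needed. The interval will be wider than one based on individual-level degrees of freedom: with 13 degrees of freedom the t multiplier is 2.16 rather than 1.99, about 9% more (2.16/1.99 = 1.09). That width reflects the cluster design. The change should be presented as better targeting of the endpoint, not as a gain in power.

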#### Randomisation

People with MS will be assigned to occupational therapists, based on geographic location, and the occupational therapists will be randomly assigned to one of two study arms (i.e. COB-MS delivery or wait-list control), using 1:1 allocation, via randomised block permutation. Notably, cluster randomisation was the most appropriate randomisation strategy for this trial, given the potential for contamination in an individually randomised trial. A web-based clinical trial randomisation service will be used (Sealed Envelope). An independent, unblinded researcher will conduct the randomisation, having been provided information regarding sequence and type of randomisation to be used (as described above) by the statistician (who is not involved in participant allocation). Participants will be informed of their allocation by an unblinded research assistant, through post and phone call. Participants’ details will be passed to their allocated occupational therapists to initiate contact and the intervention.

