Session 6, week 6, group	***Focus on Doing*** • How are our occupations and daily life affected? • What we can do to help: integrate what has been covered to date and strategies that might be helpful • Give clear examples of how to adapt or remediate occupations
Session 7, week 7, group	***Seeking New Challenges*** • Seeking new challenges • Setting goals for yourself • Keeping motivated, maintaining progress and adapting • Group conclusion and debrief
Session 8, week 9, individual	***Testing the Application*** • Review goals and strategies used • Set new goals if appropriate, plan for future • Signpost to groups and services • Debrief and summary

COB-MS will primarily be conducted in a community setting (e.g. occupational therapist’s practice or local community centre), though two individual sessions will be conducted in the participants’ own homes (or a convenient location). In total, the COB-MS group will receive approximately 2 h of one-on-one occupational therapy as well as approximately 6 h of group-based occupational therapy focused on cognitive rehabilitation. Each group session consists of a theory/background discussion regarding different aspects of cognition (≈ 10 min), related strategies (≈ 15 min), application to participants’ own life and goals (≈ 20 min) as well as opportunities to practice such evidence-based strategies (≈ 15 min). Session 1 involves an initial visit with an occupational therapist who introduces the programme and helps the participant set personal goals.

Sessions 2–7 are once-weekly group sessions with a small group (i.e. seven to nine participants with MS). Session 8 is a final, individual session that takes place 2 weeks after the last group session. Acceptability interviews (not part of the treatment) will take place within 2 weeks of intervention completion in order to control for cognitive difficulties affecting recall.

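### Therapists are randomised and the sample is inflated for therapist clustering, but the named 2 × 4 mixed ANOVA has no therapist term, so efficacy p-values and intervals are too optimistic wherever clustering enters the contrast

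*Protocol article*

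**What the plan says.** All places are in the protocol article, under Methods.

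- **Randomisation.** Participants are attached to therapists by location, and "the occupational therapists will be randomly assigned to one of two study arms", "using 1:1 allocation, via randomised block permutation". The therapist is the randomised unit.
- **Sample size.** Correlation within therapist is accepted: "assuming 8 participants per cluster (occupational therapist) and an intracluster correlation coefficient (ICC) = 0.05". From this, "the sample size becomes 90 × [1 + (8–1) × 0.05] = 121" and "the number of occupational therapists needed is 121/8 = 15", giving 15 × 8 = 120 participants.
- **COB-MS (experimental) condition.** Six of the eight sessions are delivered to a "small group (i.e. seven to nine participants with MS".
- **Control condition.** Controls are offered the programme only once data collection is over.
- **Statistical analysis.** Primary and secondary outcomes are compared by "a series of 2 (condition) × 4 (time) mixed (multivariate) analyses of variance", together with correlational analysis. No therapist effect, cluster-level summary or cluster-robust standard error is named, and no significance level is given.

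**The concern.** In a 2 (condition) × 4 (time) design, the word mixed means one between-participant factor and one within-participant factor. Such an analysis handles repeated measurements on a person. It does not handle people who share a therapist. Its between-participant error term has about 120 − 2 = 118 degrees of freedom, although 15 units were randomised, which leaves 15 − 2 = 13.

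The sample therefore pays for clustering and the analysis then ignores it. The method is named, so this is a choice the protocol has fixed and not a detail left to the statistical analysis plan.

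The consequence is overstated precision for preliminary efficacy. That is a stated objective, its results are to be published in either direction, and outcomes are among the areas listed under Progression criteria.

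Nothing elsewhere repairs this. The participant ratings of therapists, meant to control for therapist performance, are anonymous, pooled and collected only at the end of COB-MS, so they cannot stand in for a therapist term.

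**Working it through.** **Inputs from the protocol article.** 15 therapists, taken as 8 intervention and 7 control under 1:1 allocation; m = 8 per cluster (7 to 9 in delivery); ICC = 0.05, set for retention; four time points.

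**Assumptions.** Two-sided 5% test; the retention ICC carried over to the efficacy outcomes; within-person correlation of 0.6 in the repeated-measures simulations.

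**1. The protocol's own figure.** Design effect = 1 + (8 − 1) × 0.05 = 1.35. Then 90 × 1.35 = 121.5 (stated 121) and 121.5 / 8 = 15.2 (stated 15). It reproduces.

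**2. Comparison at one visit, both arms clustered.** The correct SE is √1.35 = 1.162 times the SE that ignores clusters, so the latter is too small by 1 − 1/1.162 = 13.9%. Actual error rate = 2 × [1 − Φ(1.96 / 1.162)] = 9.2%. Simulation (8 + 7 clusters of 8, 40,000 runs) gives 9.3%. A t test on the 15 therapist means (13 df) gives 5.1%.

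Sensitivity by the same formula:

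| ICC | m | Error rate |
|---|---|---|
| 0.01 | 8 | 5.8% |
| 0.02 | 8 | 6.6% |
| 0.05 | 7 | 8.6% |
| 0.05 | 8 | 9.2% |
| 0.05 | 9 | 9.8% |
| 0.10 | 8 | 13.3% |

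**3. Comparison at one visit, only the intervention arm clustered.** Variance ratio = (1.35/64 + 1/56) / (1/64 + 1/56) = 1.163; its square root is 1.079; error rate = 2 × [1 − Φ(1.96 / 1.079)] = 6.9%. Simulation gives 6.9%. With 7 intervention and 8 control clusters the ratio is 1.187 and the rate 7.2%.

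**4. Condition × time.** A therapist effect that is the same at all four visits cancels from within-person contrasts. One that appears after baseline does not. Simulation at ICC 0.05, 8,000 runs per row, post-baseline effect shared by the three later visits:

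| Where clustering acts | Univariate test | Multivariate test |
|---|---|---|
| Both arms, constant over time | 5.1% | 5.5% |
| Intervention arm only, after baseline | 7.5% | 7.3% |
| Both arms, after baseline | 9.9% | 9.1% |

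Separate 6,000-run simulations gave 6.8–6.9% for the second row and 9.2–9.6% for the third. At ICC 0.10 the 8,000-run set-up gives 9.6–9.7% (intervention arm only) and 14.1–15.3% (both arms).

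**5. Does a cluster-level analysis hold its level?** A t test on therapist mean change from baseline to 12 weeks gives 4.8–5.0% in all three settings of step 4.

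**6. Would a random therapist intercept alone be enough?** Not for condition × time. A constant intercept drops out of within-person contrasts just as the participant intercept does. When that model was fitted to balanced data with a post-baseline cluster effect, its condition × time F agreed with the ordinary ANOVA F to within 0.002 in 60 of 60 data sets, although some fits gave convergence warnings.

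**The case against.** The best defence accepts the mismatch and limits its reach. Most of it stands.

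- **Mechanism.** A reader might infer that the group format inflates every between-arm test to about 9%. The documents do not support that. Controls attend no COB-MS groups before data collection ends, so group-induced clustering arises in the intervention arm only, which gives about 7% for condition × time. Clustering that reaches both arms from the outset is mainly geographic. If it is stable over time it cancels from condition × time and affects only comparisons of level. The 9% for condition × time needs clustering that arises after baseline in untreated controls as well.
- **More extreme figures.** Rates of 14% to 24% for condition × time can be produced by letting each therapist's effect vary independently from visit to visit in both arms. Nothing in the protocol points to such a pattern.
- **Borrowed inputs.** The ICC of 0.05 was chosen for a retention proportion. None is given for goal attainment or the cognitive scores. The 5% level is convention; the protocol states none.
- **Feasibility purpose.** Efficacy is preliminary, no p-value threshold is attached to progression, and the definitive trial is to be sized from means and SDs. This lowers the stakes, but it does not make the named analysis fit the design.
- **Retention interval.** A reader might also infer that the retention interval ignores clustering. The text says only "The retention rate will be estimated using a 95% confidence interval (CI") and fixes no method. A cluster-adjusted interval is not excluded, so there is no error to report there.

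**Conclusion.** The point holds as a mismatch between design and named analysis: the ANOVA omits the randomised unit, and its efficacy SEs and p-values are anti-conservative wherever therapist or group clustering enters the contrast.

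Under the stated assumptions, a comparison at one visit has an error rate of about 9% (both arms clustered) or 6–7% (intervention arm only). Condition × time runs from about 5% (constant effect), through about 7% (post-baseline, intervention arm only), to about 9% (post-baseline, both arms). The figures move with the true ICC, which the protocol does not give for these outcomes. It would be wrong to say that every between-arm test is inflated.

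This should be corrected before analysis. It concerns the reliability of preliminary efficacy results; it does not undermine the feasibility outcomes.

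**What to change.** Replace the ANOVA wording with one of the following for each outcome:

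- a linear mixed model with condition, time and their interaction, random therapist **and** therapist-by-time effects, repeated measures within participant, and a small-sample degrees-of-freedom correction (Kenward–Roger or Satterthwaite, about 13 df between clusters); or
- a cluster-level analysis of therapist means, or of therapist mean changes from baseline, which holds about 5% in simulation.

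A therapist intercept without the therapist-by-time term is not sufficient (step 6).

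The cost is analysis wording only. Participants are assigned to therapists, so cluster membership should be known; the team should confirm that it is kept in the analysis data set. Design and sample size do not change. At ICC 0.05 intervals widen by about 16% (√1.35 = 1.162). The move from 118 to 13 df adds a factor of 2.160 / 1.980 = 1.09, so about 1.162 × 1.09 = 1.27 in all for a single-visit comparison with both arms clustered.
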